#### Imaging procedures

All patients scanned on a 3 T wide bore scanner (Skyra, Siemens, Erlangen, Germany) using a 20-channel head and neck coil (Fig. 2). Morphological and functional sequences are obtained in the same scan session.

**Fig. 2 Fig2:**
[figure not shown]
Research scan patient setup for MRI in MPHNC study

##### Morphological MRI

Sagittal T2 TIRM (turbo inversion recovery magnitude).

Axial T2 TSE DIXON water-only.

Coronal T2 TSE DIXON water-only.

Axial T1 DIXON water-only, pre- and post-contrast.

##### Functional MRI

Coronal BOLDGradient echo imaging with multiple echoes5 mm slice thickness, 2 averages, 8 slices through region of interestIn-plane resolution 1.7 × 1.7 mmTR 500 ms, TE 2.46 to 56.58 ms (12 echoes, 4.92 ms spacing)

Axial DWIReadout segmentation of long variable echo-trains (RESOLVE) sequence3 mm slice thicknessIn-plane resolution 0.4 × 0.4 mm3-scan trace, monopolarb = 50 s/mm^2^ with one average, b = 800 s/mm^2^ with 3 averages, calculated image at b = 1400 s/mm^2^
Bandwidth 868 Hz/Px

Repeat coronal BOLDGradient echo imaging with multiple echoes5 mm slice thickness, 2 averages, 8 slices through region of interestIn-plane resolution 1.7 × 1.7 mmTR 500 ms, TE 2.46 to 56.58 ms (12 echoes, 4.92 ms spacing)

DCE scans2 x 3D coronal T1 VIBE (volumetric interpolated breath-hold examination) scans for T1-mapping2° and 15° flip angles3 mm slice thicknessIn-plane resolution 1 × 1 mmAcquisition time 1 m 21 sBandwidth 440 Hz/Px
TWIST (Time-resolved angiography With Interleaved Stochastic Trajectories)Slice thickness 3 mmIn-plane resolution 1 × 1 mmTR 3.06 ms, TE 1.35 msBandwidth 800 Hz/Pxi.v. gadobutrol (Gadovist, Bayer) 0.1 mL/kg, capped at a maximum of 7.5 mL; injection of contrast immediately before 4th measurement, 4 ml/s with 20 ml saline flushScan for total 60 timepoints, temporal resolution 5.64 sData acquired for 5 m 33 s

Hop on hop off sub-study scans (week −3 to 0 only)Patients who consent to the sub-study get up from the couch and are repositioned a few minutes laterAxial T1, T2 and DWI scans are repeated

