### Imaging

#### Imaging schedule

Functional MRI studies are carried out prior to commencing treatment, then weeks 2, 3, 5 and 6 during treatment, followed by 1 month and 3 months post-treatment (Fig. 1).

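### The only contrast-allergy exclusion names Gd-DTPA, while the agent injected for DCE-MRI is gadobutrol

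*Protocol article*

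**What the plan says.** Four places in the protocol article bear on this.

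- **Functional MRI, DCE scans.** The agent and dose are "gadobutrol (Gadovist, Bayer) 0.1 mL/kg", with an upper limit of 7.5 mL. The Morphological MRI section also lists a T1 sequence before and after contrast, but names no other agent.
- **Exclusion criteria.** The single item on contrast allergy refers to Gd-DTPA. It comes at the end of a run that opens with a general exclusion for contraindications to MRI and continues with claustrophobia, cardiac devices and implanted metal.
- **Early withdrawal of subjects.** One reason for withdrawal is developing a condition that appears in the exclusion list. Others include toxicity that is not acceptable, a request or need to stop early, and the investigator's judgement.
- **Imaging schedule.** Functional MRI takes place "prior to commencing treatment, then weeks 2, 3, 5 and 6 during treatment, followed by 1 month and 3 months post-treatment".

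**The concern.** An allergy criterion for a contrast study should name the agent the study gives, or the class it belongs to. Here it names a different one. Read item by item, a patient with a known reaction to gadobutrol does not meet the allergy exclusion, while a patient who has reacted only to Gd-DTPA, which the article never says it injects, does. The withdrawal reason that points back to the exclusion list inherits the same wording.

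What is at stake is participant safety, not inference. The contrast scans are study procedures repeated over treatment and follow-up, and DCE parameters are part of the primary endpoints, so the injection is integral to the protocol. A patient who reacts at the first scan still has further contrast scans scheduled, and that is when a clear rule is most useful.

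**Working it through.** The point is a comparison of wording. The plan states no figure to reproduce, and no power or sample-size formula applies.

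**Step 1: which agent is given.** Functional MRI names gadobutrol. No other agent is named for injection anywhere in the article. Gd-DTPA appears only in the Exclusion criteria. The Abbreviations list expands Gd as gadolinium but has no entry for DTPA, so nothing in the article defines the term as covering gadolinium agents in general.

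**Step 2: how often it is given.** From Imaging schedule: 1 session before treatment + 4 during (weeks 2, 3, 5 and 6) + 2 after (1 and 3 months) = 7. The Abstract says DCE is performed before, during and after treatment, and no visit is exempted in the text. Seven injections is therefore an upper bound per patient. It assumes DCE at every session, which Fig. 1 (not shown) might qualify. After a reaction at the first scan, up to 7 − 1 = 6 would remain.

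**Step 3: which criteria each patient meets.**

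| Patient | Allergy item, as worded | General MRI-contraindication item |
|---|---|---|
| Known reaction to Gd-DTPA | Met | Met |
| Known reaction to gadobutrol only | Not met | Met if the items after it are examples; not met if they are exhaustive |

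The second row is the mismatch. Whether the general item closes it depends on how the list is nested. The text available does not preserve nesting, so this cannot be settled. The order of the items does suggest that the allergy item belongs under the general one.

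**Step 4: withdrawal after a reaction during the study.** The reason tied to the exclusion list follows whichever reading of Step 3 applies. The reasons based on toxicity, early discontinuation and the investigator's judgement do not depend on that list, and a patient who reacts to gadobutrol can be withdrawn under any of them.

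**The case against.** The strongest reply is that the list already covers the case. The study MRI includes a gadobutrol injection, so a known gadobutrol reaction is naturally a contraindication to that MRI, and nothing says the items that follow the general one are exhaustive. On that reading both the exclusion and the linked withdrawal reason are met. Most of this stands. It is a reasonable reading and probably the one clinicians would apply. It leaves the specific item misworded all the same.

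A second reply is that Gd-DTPA may be loose shorthand for gadolinium contrast, which the Background mentions generically, and that excluding someone who has reacted to another gadolinium agent is merely cautious. That is plausible, and the caution harms no participant. But the criterion names one agent and the imaging section names another, and a reader should not have to guess that the class was meant. That the two names denote different products is general pharmacology; the article shows only that it uses two names.

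Three stronger readings are tempting, and the documents do not support them:

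- *That a patient who reacts to gadobutrol could be neither excluded nor withdrawn.* The general item and the three independent withdrawal routes contradict this.
- *That 7 × 55 = 385 injections are affected.* That product counts every scheduled injection if all 55 patients complete all sessions. The relevant group is patients with a known gadobutrol reaction who also pass the general MRI item, and the article gives no figure for it.
- *That site screening asks about the wrong product.* The screening form and MRI safety procedures are not shown. Only the wording of the published criterion can be criticised.

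**Conclusion.** The mismatch is real and minor. The one exclusion written for contrast allergy does not name the agent injected. The number of patients affected cannot be derived from the documents and is probably small, because the general MRI item and the other withdrawal routes are likely to catch most of them. There is no effect on sample size, power, error rates, endpoints or interpretation.

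The conclusion assumes that the two names refer to two different products and that the criterion is applied as worded. If the general item is read as open-ended, what remains is a wording error in an operative safety criterion, still worth correcting because the correction is so simple.

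**What to change.** Reword the item in the Exclusion criteria so that it covers a known allergic reaction to gadobutrol or to any other gadolinium-based contrast agent. Early withdrawal of subjects needs no separate edit, because the reason that refers to the exclusion list picks up the new wording. Naming the class as well as the product keeps the present caution about Gd-DTPA.

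The cost is a one-line amendment and, at most, a rare additional exclusion. No change to the sample size or analysis is needed.

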### Statistical plan

#### Sample size determination

Based on our previous study using week 3 FDG-PET scan in head and neck cancer patients, the following sample size calculation is made. To test a significant FDG-PET complete metabolic response (CMR) rate of 87% in the MRI-positive group versus an FDG-PET CMR rate of 51% in the MRI-negative group, the study will need to recruit 55 patients in total to reach 80% power (at 5% significance level). This number is based on an assumption that the MRI-positive group and MRI-negative group will be balanced (e.g. 50%:50% but is powered to allow up to a 40%:60% biased ratio). It is anticipated that recruitment will be completed in 24 months. Patients will be offered participation in the “hop on hop off” sub-study, with a recruitment goal of 20.

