### Objectives

#### Primary objective

To determine the correlation of pre-, during treatment and post-radiotherapy (± chemotherapy) functional MRI with tumour response at 3 months by FDG-PET scan and with local control at 12 months.

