### Endpoints

#### Primary endpoints

Correlation of functional MRI sequences with PET-CT at 3 months following treatment and local control at 12 months, including:Measurement of restricted water diffusion as on DWI, which can be a marker of high cellularity within a tumour, using ADC values, ΔADC and parameter maps of ADC.Measurement of tumour perfusion characteristics from DCE-MRI, using parameter maps and calculated values based on inflow and outflow (K^trans^, K_ep_) as well as degree of contrast enhancement of tissues (Relative Signal Intensity, RSI).Tumour size as defined on anatomical imaging using T2-weighted and/or T1-weighted Volume Interpolated Breathhold Examination (VIBE) Dixon MRI.

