##### BOLD

A reduction in R2* values will be considered a good response (positive MRI) and either no change or increase in R2* values will be considered a poor response (negative MRI).

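### The 80% power and 5% level belong to one MRI-positive versus MRI-negative test that the protocol never identifies; they do not cover its multi-part primary objective

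*Protocol article*

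**What the plan says.** **Sample size.** The protocol's section on sample size determination describes one comparison of two proportions: "To test a significant FDG-PET complete metabolic response (CMR) rate of 87% in the MRI-positive group versus an FDG-PET CMR rate of 51" (per cent, the rate assumed for MRI-negative patients). It concludes that "the study will need to recruit 55 patients in total to reach 80% power (at 5% significance level"), with groups assumed to be "50%:50% but is powered to allow up to a 40%:60% biased ratio". No sequence, parameter or scan time is attached to the terms MRI-positive and MRI-negative.

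**Primary objective and endpoints.** The primary objective relates pre-, during- and post-treatment "functional MRI with tumour response at 3 months by FDG-PET scan and with local control at 12 months". The primary endpoints repeat both outcomes ("Correlation of functional MRI sequences with PET-CT at 3 months following treatment and local control at 12 months") and list ADC, change in ADC, ADC maps, K^trans, K_ep, relative signal intensity and tumour size.

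**Scans.** The imaging schedule has seven MRI times: baseline, weeks 2, 3, 5 and 6, and 1 and 3 months after treatment.

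**Response rules.** The section on assessment of MRI sequences gives three separate rules. DWI is positive when ADC is high, with no cut-off. DCE is positive when inflow and outflow fall. The BOLD rule is: "A reduction in R2* values will be considered a good response (positive MRI"). Nothing says how to classify a patient who is positive on one sequence and negative on another.

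**Analysis.** The statistical analysis section sets p < 0.05 throughout. It assigns the chi-square test to complete metabolic response (CMR) by MRI group, and kappa with sensitivity and specificity to CMR and 12-month local control. It uses ROC curves to find an optimal threshold for each MRI parameter. It names no primary test, testing order or adjustment.

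**The concern.** A power statement means something only for an identified test. Here the sized comparison could be run on DWI, DCE or BOLD, on several parameters within each, and at up to seven times. The protocol's own lists do not settle which:

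- BOLD has a response rule for endpoint analysis but is not among the primary endpoints.
- Relative signal intensity and tumour size are primary endpoints but have no response rule.
- Correlation with 3-month PET response and 12-month local control appears under both the primary and the secondary endpoints.

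With one unadjusted threshold, the sequence and time that become the headline could be chosen after the results are seen. The protocol hypothesises that functional MRI is a reliable biomarker and an alternative to FDG-PET, and its Discussion says the findings will feed into the design of interventional adaptive-radiotherapy studies. A chance finding could therefore be carried into a treatment trial.

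**Working it through.** **1. Reproduce the plan's figure.** Inputs from the sample size section: p₁ = 0.87, p₂ = 0.51, power 80%, level 5%. Sidedness is not stated, so two-sided is assumed. With k = n₂/n₁ and p̄ = (p₁ + k·p₂)/(1 + k):

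n₁ = [1.96·√((1 + 1/k)·p̄(1 − p̄)) + 0.8416·√(p₁(1 − p₁) + p₂(1 − p₂)/k)]² / (p₁ − p₂)²

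- 50:50 (k = 1, p̄ = 0.69): n₁ = 24.7, rounded up to 25; total 50.
- 40% positive, 60% negative (k = 1.5, p̄ = 0.654): n₁ = 20.98, rounded up to 21; total 53.

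The stated 55 is within two patients of 53. Exact enumeration of the uncorrected chi-square test with 55 patients gives power of 85% at 28:27 and 83% at 22:33. The calculation is sound for one test.

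**2. Count the tests on a narrow reading.** The number of primary tests is not fixed by the document, so this count is an assumption. Take only the two functional sequences listed as primary endpoints (DWI, DCE), one parameter each, the six post-baseline scans, and CMR only: 2 × 6 × 1 = 12 tests. This leaves out BOLD, tumour size, the baseline scan, further parameters and local control.

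**3. Chance of at least one false positive if MRI predicts nothing.** Twelve independent tests at exactly 5% give 1 − 0.95¹² = 46%. A chi-square test on so small a table rejects slightly less often than 5%, so this was simulated. The settings were 55 patients, 17 without CMR, a pre-fixed median split for each reading, and a common correlation between readings. The 17 follow from 28 × 0.87 + 27 × 0.51 = 38.1 expected CMRs. The correlations are assumed, because the protocol gives none.

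| Assumed correlation | At least one p < 0.05 |
|---|---|
| 0 | 41–42% |
| 0.5 | 34% |
| 0.7 | 27–28% |

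The ranges show differences between simulation runs. At correlation 0 each test rejected about 4.35% of the time, and 1 − (1 − 0.0435)¹² = 41%, which agrees. These figures use cut-offs fixed in advance. Thresholds chosen by ROC in the same patients would add inflation that is not counted here.

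**4. Power if the 5% is protected.** Splitting alpha across three sequences gives 0.05/3 = 0.0167 per test. Exact chi-square power with 55 patients:

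| Split (positive:negative) | Level 0.05 | Level 0.0167 |
|---|---|---|
| 28:27 | 85% | 72% |
| 22:33 | 83% | 69% |

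The normal-approximation formula gives 70% and 66% at the smaller level. By the same formula, restoring 80% power would need 68 patients at 50:50 or 73 at 40:60.

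**The case against.** **The study is exploratory in character.** It is a single-arm observational imaging study with no treatment intervention. Finding the best scan time is a stated secondary objective, and the Discussion presents the search across sequences and times as a purpose of the work. This stands as a reason not to demand adjustment of every analysis. It does not explain a formal 80% power claim attached to an unidentified test, and the protocol does not call its primary objective exploratory.

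**A statistical analysis plan may settle it.** A separate plan, not shown, could name one test or an adjustment, and silence on that alone would be no finding. However, the protocol already fixes a multi-part primary objective and a blanket p < 0.05. A later plan would have to override that text, not merely fill it in.

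**Stronger readings that a reader might infer.**

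- *That 55 is the wrong number.* It is not; it reproduces for one test.
- *That error is near-certain.* Three sequences × six scans × two outcomes gives 36 tests and 1 − 0.95³⁶ = 84%. The document does not support that figure. BOLD is not a listed primary endpoint, local control has no named significance test, and repeated scans of the same tumour are not independent.
- *That the calculation points to week-3 MRI.* The week 3 mentioned in the sample size section is an FDG-PET scan from an earlier study, so it does not identify an MRI time.

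**Conclusion.** The concern holds in a limited form. The 80% power and 5% level are valid for one prespecified comparison of CMR between MRI-positive and MRI-negative patients. The protocol never defines that comparison, and the figures do not hold for the primary objective as a whole. On a narrow count of 12 tests, the chance of at least one false-positive result is about 27–42% rather than 5%.

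That range rests on an assumed test count, assumed correlations of 0.7 to 0, and median splits fixed in advance. Stronger correlation would lower it; ROC-chosen thresholds, more parameters or more sequences would raise it. The finding that the primary test is unidentified rests on none of these assumptions.

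**What to change.** 1. Before outcome data are examined, the sponsor names one sequence, one parameter, one scan time and a pre-fixed cut-off, tested against CMR on the 12-week FDG-PET, as the single primary test that the 55 patients are sized for. The choice is the sponsor's. If change in ADC is chosen, it must be reconciled with the present DWI rule, which uses high ADC values and gives no cut-off.
2. Label all other sequences, parameters, times and outcomes, including 12-month local control, secondary or exploratory. Report them with confidence intervals and multiplicity-adjusted p-values.
3. Remove the secondary endpoint that repeats the primary one.
4. If several primary sequences are kept, split alpha and restate the power. For three sequences with 55 patients this is about 72% at 50:50 and 69% at 40:60.

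**Cost.** Naming one test needs changes to protocol and analysis-plan wording only, with no extra patients. The price is that other sequences and times can no longer be claimed as primary results.

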#### Assessment of MRI sequences

MRI scans will be determined as a good response (e.g. positive) or poor response (e.g. negative) based on the following definitions for endpoint analysis:

##### DWI

High ADC values will be considered a good response (positive MRI) and low ADC values a poor response (negative MRI).

##### DCE MRI

A reduction in blood inflow and outflow (e.g. K^trans^ and K_ep_) will be considered a good response (positive MRI) and either no change or an increase will be considered a poor response (negative MRI).

##### BOLD

A reduction in R2* values will be considered a good response (positive MRI) and either no change or increase in R2* values will be considered a poor response (negative MRI).

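### The DCE and BOLD rules call any fall, however small, a good response, so measurement error helps decide the class, and they cannot class the pre-treatment scan

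*Protocol article*

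**What the plan says.** The section Assessment of MRI sequences presents its rules as the definitions to be used in the endpoint analysis. There are three:

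- **BOLD:** "A reduction in R2* values will be considered a good response (positive MRI) and either no change or increase in R2* values" are a poor response (negative MRI).
- **DCE MRI:** a reduction in inflow and outflow, with Ktrans and Kep as examples, "will be considered a good response (positive MRI) and either no change or an increase will be considered a poor response".
- **DWI:** scored on level, not change: "High ADC values will be considered a good response (positive MRI"), with low values negative.

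Statistical analysis compares the complete metabolic response (CMR) rate on FDG-PET between MRI-positive and MRI-negative groups by chi-square. That comparison sizes the study: "To test a significant FDG-PET complete metabolic response (CMR) rate of 87% in the MRI-positive group", set against 51% among MRI-negative patients. On these rates, "the study will need to recruit 55 patients in total to reach 80% power (at 5% significance level"). The groups are taken as "balanced (e.g. 50%:50% but is powered to allow up to a 40%:60% biased ratio"). The same section also plans an ROC-derived threshold for individual MRI parameters.

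The Primary objective covers MRI before, during and after treatment. The Primary endpoints list DWI, DCE and tumour size, but not BOLD.

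**The concern.** R2*, Ktrans and Kep are continuous measurements with error. On such a scale an exact result of no change hardly ever occurs, so in practice the rule reads only the sign of the observed difference. A small fall produced by noise counts the same as a large true fall. Poor responders who cross zero by chance join the positive group and bring its CMR rate towards that of the negative group. The chi-square contrast then shrinks.

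Three gaps follow from the same wording:

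- A change rule needs an earlier scan, so it gives no class to the pre-treatment scan.
- The DCE rule names two quantities and does not say what happens when they move in opposite directions.
- The ROC threshold is a second cut on the same parameters, and the text does not say which cut forms the chi-square groups.

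**Working it through.** **Inputs.** From Sample size determination: CMR 87% and 51%, N = 55, power 80%, significance level 5% (two-sided assumed, as sidedness is not stated), split 50:50 and at most 40:60. Assumed, because the document gives no measurement error: the share *f* of true poor responders who show a fall by noise alone.

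**1. The plan's own figure.** Pooled-variance formula for two proportions, no continuity correction, with k = negative:positive ratio:

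n(positive) = [1.96·√((1+1/k)·p̄·q̄) + 0.8416·√(p1·q1 + p2·q2/k)]² / (p1 − p2)²

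- k = 1: p̄ = 0.69; (1.2820 + 0.5071)² / 0.1296 = 24.7, so 25 per group and 50 in total.
- k = 1.5 (40% positive): p̄ = 0.654; (1.2037 + 0.4451)² / 0.1296 = 20.98, so 21 + 32 = 53.

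The stated 55 is within 2 of the 40:60 result. Exact power of the uncorrected chi-square test at N = 55 is 0.85 at 28:27 and 0.83 at 22:33. The sample size is sound on its own inputs.

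**2. The zero cut.** Let the observed change be normal around the true change. The chance of an observed fall is Φ(−δ), where δ is the true increase in units of the SD of the difference.

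- δ = 0: 50%
- δ = 0.5: 31%
- δ = 1: 16%

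**3. Dilution.** Assume a true 50:50 split, treat 87% and 51% as error-free rates, and let no good responder be mislabelled.

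- Positive share = 0.5 + 0.5f
- CMR in positives = (0.5 × 0.87 + 0.5f × 0.51) / (0.5 + 0.5f)
- CMR in negatives stays at 0.51

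| f | Positive share | CMR in positives | Groups | Exact power |
|---|---|---|---|---|
| 0 | 50% | 87.0% | 28:27 | 0.85 |
| 10% | 55% | 83.7% | 30:25 | 0.74 |
| 20% | 60% | 81.0% | 33:22 | 0.67 |
| 50% | 75% | 75.0% | 41:14 | 0.42 |

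The normal approximation gives 0.75, 0.66 and 0.39 for the last three rows.

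**4. Imbalance alone.** If 5% of good responders are also mislabelled at f = 50%, the positive share is 0.5 × 0.95 + 0.5 × 0.5 = 72.5%, a split of about 73:27. With the rates held at 87% and 51%, exact power at 40:15 is still 0.82. The loss in step 3 therefore comes from the shrunken contrast, not from the split.

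**5. Discordant DCE, read jointly.** With no true change in either parameter and error correlation ρ, the two signs disagree with probability arccos(ρ)/π: 50% at ρ = 0, 33% at 0.5, 20% at 0.8 and 14% at 0.9. These correlations are assumed.

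**6. Pre-treatment scan.** The Primary objective and the Imaging schedule both include it. The DCE and BOLD rules score a reduction, and before treatment there is no earlier scan to reduce from. Only the DWI level rule can be applied there.

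**The case against.** The case against has weight on several points.

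- **Rates as classified.** The 87% and 51% are stated for the MRI-positive and MRI-negative groups, so they may already carry some classification error. Adding more could count it twice. This stands, and it makes the power figures illustrations.
- **The 50% scenario is extreme.** It needs every poor responder to have no true change. The rules also place increases in the poor class, and those tumours cross zero less often. This stands too.
- **The group split.** A reader might infer that noise pushes the split outside 40:60 and that this costs the power. The split can leave that range, but 73:27 alone keeps power at 0.82. A 20:80 positive:negative split does lower power to 0.64, but it runs opposite to a mechanism that adds positives.
- **Discordant DCE.** A reader might infer that discordant patients fit no class at all. The parameters are given as examples, and Statistical analysis speaks of individual parameters; read one at a time, no discordance arises. Read jointly and strictly, everything short of a double fall could be negative. The text settles on neither reading.
- **Pre-treatment scan.** Baseline values can still be analysed as continuous measures or through an ROC cut. Only the positive/negative label is unavailable.
- **ADC.** A reader might see a contradiction because change in ADC is a listed primary measure. ADC values are listed as well, so the level rule contradicts nothing.
- **Detail for a fuller document.** A tolerance might be set there. But the article does not leave the cut open: it fixes it at zero as an endpoint definition.

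The ROC threshold does not answer the point, because nothing says that it replaces the zero cut.

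**Conclusion.** The point holds in limited form. The DCE and BOLD rules fix the cut at zero change, so measurement error can decide the class of a tumour that changes little. They give no label to the pre-treatment scan, state no class for discordant Ktrans and Kep under a joint reading, and stand beside an ROC threshold of unstated role. The consequence is clearest for DCE, because BOLD is not a listed primary endpoint.

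The size is conditional: power of 0.74, 0.67 or about 0.4 against 0.85, for 10%, 20% or 50% of poor responders crossing zero. This assumes error-free rates of 87% and 51%, a true 50:50 split and errors in one direction only. The document has no measurement-error figure with which to choose among these. It does not support the stronger conclusions that the study is underpowered or that 55 is wrong. The change is worth making because a better analysis is available from data already being collected.

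**What to change.** 1. For each DCE and BOLD parameter separately, use percentage change from the patient's own baseline as a continuous predictor of CMR at every on-treatment and post-treatment scan: logistic regression, odds ratio per SD, and AUC with confidence interval.
2. For the pre-treatment scan, use the baseline value itself as the predictor.
3. Where a binary class is kept, state one cut that forms the chi-square groups, and say what role the ROC threshold then has.
4. For a binary R2* class, require a fall beyond the repeatability limit estimated from the repeat BOLD run already in each session. Note that this limit is a minimum, since a within-session repeat excludes repositioning and between-visit error.
5. Keep DCE continuous. It has no repeat scan, and the hop on hop off sub-study repeats only T1, T2 and DWI.

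The cost is a rewrite of two short rules and slightly more analysis, with no new scans. The remaining weakness is that DCE has no repeatability limit.
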